## METHODS

### Study design and setting

This is a prospective, observational cohort study, that will be conducted by the Fourth Internal Medicine Department at Hippokrateion General Hospital of Thessaloniki in collaboration with the Second Medical Department of the same hospital.

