### Inclusion criteria

This study enrols adult patients with an established diagnosis of RA according to the American Rheumatism Association 1987 Revised Criteria,^45^ who are eligible for treatment with JAK inhibitors (tofacitinib, baricitinib or upadacitinib) for first time, irrespective of previous administration of conventional or biologic DMARDs based on international recommendations (EULAR 2020).^15^

Exclusion criteria include: age <18 years, inability to comprehend and sign the informed consent, previous exposure to JAK inhibitors, concomitant active malignancy or other disease with poor prognosis, recent major adverse cardiovascular event (myocardial infarction, unstable angina, stroke) within the past 6 months, and stage III–IV heart failure according to the New York Heart Association (NYHA) criteria.^46^

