### Study overview

RA patients eligible for treatment with JAK inhibitors who will be selected on the basis of inclusion and exclusion criteria to participate in the research protocol will undergo the following procedures, before the initiation of JAK inhibitors:
Recording of medical history and current medical treatmentAnthropometric measurements, clinical examination and assessment of disease severity with calculation of DAS28 (Disease Activity Score in 28 joints)Evaluation of functional ability and quality of life through specifically designed questionnairesOffice blood pressure recordingEstimation of 10-year cardiovascular riskVideocapillaroscopy of the nailfold capillary networkAssessment of 24h blood pressure, its day- to night-time variation and haemodynamic parameters with the Mobil-O-Graph deviceBlood sampling, centrifugation and thawing of the supernatant

All patients will be re-evaluated and the above procedures will be repeated at 3 and 6 months following the baseline visit, whilst the patients are under treatment with JAK inhibitors.

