## STATISTICAL METHODS

Data analysis will be performed using SPSS (Statistical Package for Social Sciences, SPSS Inc., Chicago, IL, USA) software, version 22. Results will be expressed as frequencies for qualitative variables, and as mean±standard deviation (m±SD) or median (interquartile range) for continuous variables. Comparisons of variables will be performed between the baseline and the follow-up visits. Comparison of frequencies will be performed by Pearson chi-square test. Comparison of differences between mean values will be performed with Student’s t-test or Mann–Whitney test. Correlations between the main continuous variables will be assessed using the parametric Pearson or the nonparametric Spearman’s Rho correlation coefficient. Linear regression and logistic regression analysis will be performed to investigate whether treatment with JAK inhibitors is associated with NVC parameters and parameters obtained from 24h ambulatory blood pressure recording after adjustment for other variables. A probability value of p≤0.05 will be considered statistically significant.

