Besides, evaluation of changes in patients’ haemodynamic profile and circulating biomarkers of thrombotic predisposition will point towards underlying pathophysiological mechanisms mediating cardiovascular effects of JAK inhibitors in RA. Considering the innovative study design, our results will most probably have an international impact following their dissemination in conferences and the press and their publication in peer-reviewed journals.

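### The planned regression has no estimable JAK-inhibitor term at any single visit; with visits stacked the term is only follow-up versus baseline, and ordinary regression misstates its standard error

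*Protocol article*

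**What the plan says.** Study design and setting: "This is a prospective, observational cohort study". No untreated or other-treatment group is described anywhere in the article.

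Inclusion criteria: patients enter "who are eligible for treatment with JAK inhibitors (tofacitinib, baricitinib or upadacitinib) for first time", and "previous exposure to JAK inhibitors" is an exclusion.

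Study overview: all assessments are made "before the initiation of JAK inhibitors", then repeated at 3 and 6 months while patients are on the drug.

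Statistical Methods: variables are compared between baseline and follow-up visits by Pearson chi-square, Student's t-test or Mann–Whitney. Linear and logistic regression are then planned "to investigate whether treatment with JAK inhibitors is associated with NVC parameters and parameters obtained from 24h ambulatory blood pressure recording", adjusted for other variables that are not named. No method for repeated measurements on the same patient is mentioned.

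**The concern.** A regression coefficient for treatment needs some rows with treatment and some without. Here that contrast exists only between visits of the same patient, so the term either cannot be estimated (one visit at a time) or is a before/after indicator fitted to correlated rows (visits stacked). The models named assume independent rows.

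This is the only adjusted analysis in the article, and it covers parameters that supply three of the four primary outcomes (24h BP, arterial stiffness, capillary microangiopathy). Two things are at stake. With 30–50 patients, a real change in blood pressure or microvasculature could be missed through an inflated standard error. And the coefficient could be reported as an adjusted effect of treatment, which a cohort without a comparator cannot supply.

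**Working it through.** **Inputs from the article.** One cohort; treatment = 0 for all at baseline and 1 for all at 3 and 6 months (Inclusion criteria, Study overview); n = 30–50 (Sample size); significance at p ≤ 0.05 (Statistical Methods; two-sided assumed). The sample size comes with no effect size, SD or power, so there is no planned figure to reproduce.

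**Assumed.** Within-patient correlation ρ is not given. I use 0.3 to 0.8, the same between any two visits, understood as the correlation left after covariates. A shift of 0.3 SD is assumed for the power illustration. The arithmetic is for linear regression; logistic regression was not calculated.

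**Step 1: can the term be estimated?** Take an intercept, a treatment indicator and two covariates (4 columns).

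- Baseline only: the treatment column is all zeros. Rank 3.
- 3 months only, or 6 months only: it duplicates the intercept. Rank 3.
- Change scores with a treatment column added: it duplicates the intercept. Rank 3.
- All visits stacked, with intercept, treatment and both follow-up visit indicators: 4 columns, rank 3. Treatment is the sum of the two visit indicators.

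So the term is estimable only on stacked visits, and there it means follow-up versus baseline and nothing more.

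**Step 2: standard error on stacked visits.** The estimate is the mean of the two follow-up values minus baseline.

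- Ordinary regression takes its variance as s²(1/n + 1/(2n)) = 1.5 s²/n.
- The true variance is (s²/n)[(1+ρ)/2 + 1 − 2ρ] = 1.5 s²(1−ρ)/n.
- The standard error is therefore overstated by 1/√(1−ρ), and the real type I error is 2[1 − Φ(1.96/√(1−ρ))].

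For a covariate that is constant within a patient, three rows give a design effect of 1 + 2ρ and a real type I error of 2[1 − Φ(1.96/√(1+2ρ))].

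| ρ | SE overstated by | Real alpha, treatment term | Design effect, patient-level covariate | Real alpha, covariate |
|---|---|---|---|---|
| 0.3 | 1.20 | 0.019 | 1.6 | 0.12 |
| 0.5 | 1.41 | 0.0056 | 2.0 | 0.17 |
| 0.7 | 1.83 | 0.0004 | 2.4 | 0.21 |
| 0.8 | 2.24 | 0.00001 | 2.6 | 0.22 |

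Simulation (4,000 replicates) agrees. At ρ = 0.5 the treatment term rejects in 0.6% and the covariate in 16.9% of replicates, for n = 30 and for n = 50. At ρ = 0 both reject in about 5%.

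**Step 3: power for a shift of 0.3 SD.** With the correlation modelled, power is Φ(0.3/SE − 1.96), where SE = √(1.5(1−ρ)/n) in SD units. With ordinary regression on stacked rows it is Φ[(0.3 − 1.96√(1.5/n))/SE].

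Worked for n = 50, ρ = 0.5: SE = √0.015 = 0.1225. Correct power: 0.3/0.1225 − 1.96 = 0.49, giving 0.69. Stacked: 1.96√0.03 = 0.3395, and (0.3 − 0.3395)/0.1225 = −0.32, giving 0.37.

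| n | ρ | Correlation modelled | Ordinary, stacked |
|---|---|---|---|
| 30 | 0.5 | 0.48 | 0.19 |
| 30 | 0.7 | 0.69 | 0.13 |
| 50 | 0.5 | 0.69 | 0.37 |
| 50 | 0.7 | 0.89 | 0.34 |

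**The case against.** The strongest reply is that stacking is not the only route. Linear regression of each patient's change on centred covariates has one row per patient, independent rows and a valid standard error, and its intercept is the adjusted mean change. The article does not state the row structure, and a condensed article may leave model form to a fuller plan.

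Part of this stands: an adjusted change can be obtained with linear regression, so it would be wrong to say that no valid version of the analysis exists. But the article does not describe that model. It names the association with treatment as the target, and in a change-score model that is an intercept, not a treatment coefficient. The neighbouring tests, Mann–Whitney and Pearson chi-square, are for independent samples, which makes a within-patient reading unlikely. The mismatch lies in what is stated, not in detail left out. Comparing the three JAK inhibitors would give a varying term, but that is a different question.

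Two further criticisms are tempting and should not be made.

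- *Correlations.* The article says "Correlations between the main continuous variables will be assessed using the parametric Pearson or the nonparametric Spearman’s Rho correlation coefficient". A reader might infer pooling over visits, which would raise the false-positive rate for two unrelated markers (design effect 1 + 2ρ²; about 0.07 at ρ = 0.3 and 0.16 at 0.7). Pooling is stated nowhere. Correlations at a single visit validly answer the secondary objective, which asks about associations and not about change.
- *Mechanism.* Anticipated Benefits says that the evaluation "will point towards underlying pathophysiological mechanisms mediating cardiovascular effects of JAK inhibitors in RA". A reader might take this as a mediation claim resting on those correlations. The sentence concerns changes in haemodynamic profile and biomarkers, and it is a hope about benefit, not an analysis.

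**Conclusion.** The point holds: the regression as stated does not fit a single-arm before/after design. That the term cannot be estimated at one visit, and is aliased with follow-up versus baseline when visits are stacked, follows from the design alone and needs no assumption. The sizes rest on stacking, on the assumed ρ, on equal correlation between visits and, for power, on the 0.3 SD shift.

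The direction matters. A reader might infer that the analysis would produce false-positive treatment effects, or might attach the roughly 20% type I error to the treatment term. The documents do not support that. With positive within-patient correlation the treatment test is conservative, and its cost is lost power. The inflated error belongs to patient-level adjustment covariates, which are not what the regression sets out to test.

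Modelling the correlation corrects the standard errors only. Without a comparator, treatment remains inseparable from time, regression to the mean and changes in co-medication.

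**What to change.** Replace the regression sentence with a linear mixed model (a generalised mixed model or GEE for binary outcomes) with visit (0, 3, 6 months) as a fixed factor and a random intercept for patient. A change-score regression for each follow-up visit, with centred baseline covariates and one row per patient, answers the same question for continuous outcomes.

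- Adjust the main estimate for baseline covariates only. Covariates that treatment may itself change, such as DAS28 or CRP, belong in a secondary model; otherwise the visit contrast is no longer the total change on treatment.
- Report the visit contrasts as adjusted change from baseline during JAK-inhibitor treatment, not as an adjusted treatment effect.
- State that correlations are run per visit, one row per patient, or on within-patient changes, and are not pooled over visits.

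The cost is analysis wording. The measurements are already planned at all three visits, so no patients, visits or tests are added.

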## ANTICIPATED BENEFITS

Despite their clinical efficacy in alleviating symptoms and progression of RA, cardiometabolic effects of JAK inhibitors in patients with RA remain in comparison underinvestigated, especially in the long-term. JAK inhibitors may confer increased risk for circulatory disorders, specifically thromboembolic events, and adversely affect lipids and platelet count.^19^ More recent evidence shows an increased risk of major adverse cardiovascular events associated with JAK inhibitors in RA, although the underlying mechanisms remain unclear.^17^ It has been argued that the patients’ aggravated cardiovascular profile with presence of multiple CVD risk factors may account, at least partially, for this observation.^18^ Hypertension is highly prevalent in RA and contributes substantially to the increased CVD burden associated with the disease,^11^ while ambulatory blood pressure monitoring is superior to conventional blood pressure measurements in terms of CVD risk prediction.^21^ Furthermore, subclinical microvascular injury is present in patients of RA before the establishment of overt CVD^3,4,51^ and is considered as an intermediate pathophysiological process towards the development of cardiovascular complications.^6^ At the same time, large artery stiffening represents a surrogate marker of CVD with incremental predictive value beyond traditional cardiovascular risk factors.^28^ However, the impact of JAK inhibition on blood pressure including its 24h variation, and markers of micro- and macrovascular injury has not been investigated so far in patients with RA.

Therefore, shedding light on the impact of JAK inhibitors on the above critical parameters (24h BP and day-to night-time variation, arterial stiffness, microangiopathy of the dermal capillary network) and the prothrombotic markers that will be assessed, will add substantial information to the available literature regarding cardiovascular aspects of JAK inhibitors in RA. It is anticipated that our findings will have direct clinical implications. They will either highlight potential pleiotropic beneficial effects of JAK inhibitors on the cardiovascular system, or by contrast detect and highlight potential negative aspects which should be taken into consideration by treating physicians, in order to take actions targeting at their proper monitoring and management.

Besides, evaluation of changes in patients’ haemodynamic profile and circulating biomarkers of thrombotic predisposition will point towards underlying pathophysiological mechanisms mediating cardiovascular effects of JAK inhibitors in RA. Considering the innovative study design, our results will most probably have an international impact following their dissemination in conferences and the press and their publication in peer-reviewed journals.

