While microvascular endothelial dysfunction is considered inherent to the disease, patients with RA present increased prevalence of traditional CVD risk factors.^9^ Among these patients, hypertension represents the most prevalent CVD risk factor and significantly aggravates cardiovascular prognosis.^10^ Despite major implications in terms of CVD development and progression, hypertension remains largely underdiagnosed and undertreated in patients with RA.^11^ Furthermore, the impact of anti-rheumatic treatment is often neglected and needs to be further taken into consideration. Antirheumatic treatment modalities exert divergent effects on the vasculature, with positive, neutral, or even negative effects which further contribute to the CVD complications associated with RA. While these effects have been well-described or are being intensively investigated for cornerstone treatments such as corticosteroids or biologics, the vascular effects of novel antirheumatic treatments, such Janus kinase (JAK) inhibitors, remain in comparison understudied.^12,13^ Ultimately, chronic inflammation, traditional CVD risk factors and, to a different extent, specific antirheumatic treatment modalities act synergistically to form a prothrombotic microenvironment and trigger the degeneration and remodelling of the vascular architecture.

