## AIM OF THE STUDY

The present study aims to provide further insight on the effects of treatment with JAK inhibitors on blood pressure and haemodynamic parameters, microvascular function, and subclinical macrovascular injury among patients with RA. More specifically, we aim to investigate whether treatment with JAK inhibitors in patients with RA induces alterations in:
24h BP and its circadian rhythmArterial stiffness, specifically AIx and PWV which represent the most widely used markers of large artery stiffening.Microangiopathy of the nailfold capillaries.Patients’ haemodynamic profile throughout a whole 24h period (central aortic blood pressure, wave reflection, total vascular resistance)Prothrombotic markersEstimated cardiovascular risk

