## STUDY OUTCOMES

### Primary outcomes

To determine potential differences at 3 and 6 months following treatment with JAK inhibitors compared to baseline, in the following parameters: a) 24h BP, b) arterial stiffness, c) microangiopathy of dermal capillary network, d) prothrombotic markers.

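### A single-arm before-after cohort can show change after starting a JAK inhibitor, but the aim and expected conclusions claim drug effects and mediation

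*Protocol article*

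**What the plan says.** All quotes are from the protocol article.

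- **Design.** "This is a prospective, observational cohort study" (Study design and setting). Participants are RA patients "who are eligible for treatment with JAK inhibitors (tofacitinib, baricitinib or upadacitinib) for first time" (Inclusion criteria). The baseline procedures "will be repeated at 3 and 6 months following the baseline visit, whilst the patients are under treatment with JAK inhibitors" (Study overview). No comparator group is described.
- **Primary contrast.** "To determine potential differences at 3 and 6 months following treatment with JAK inhibitors compared to baseline" (Primary outcomes), applied to 24h BP, arterial stiffness, nailfold microangiopathy and prothrombotic markers.
- **Analysis.** Statistical methods compares baseline with follow-up visits. It also plans linear and logistic regression of the capillaroscopy and 24h-recording parameters on JAK inhibitor treatment, adjusted for covariates that are not named.
- **Claims.** The aim is to learn "whether treatment with JAK inhibitors in patients with RA induces alterations in" the listed parameters (Aim of the study). Anticipated benefits expects consequences for clinical practice and says of the findings: "They will either highlight potential pleiotropic beneficial effects of JAK inhibitors on the cardiovascular system, or by contrast detect and highlight potential negative aspects". Its last paragraph expects that haemodynamic and biomarker changes "will point towards underlying pathophysiological mechanisms mediating cardiovascular effects of JAK inhibitors in RA".

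**The concern.** The aim and the expected conclusions are causal, while the contrast is a patient's later value minus the same patient's earlier value. Anything else that changes over six months enters that difference.

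The document itself supplies candidates. The Introduction says that antirheumatic treatments affect the vasculature in differing directions, and that "hypertension remains largely underdiagnosed and undertreated in patients with RA". Every patient has a 24h recording at baseline, so blood pressure treatment could plausibly be started or changed between visits. A resulting fall could look like a benefit of the JAK inhibitor, or could mask a BP rise, which is the kind of harm the study is meant to detect. A p-value does not correct this.

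**Working it through.** The document gives no effect size, SD or power, so there is no stated figure to reproduce. Two checks follow.

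**1. Can the regression isolate the drug?**

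Take 30 patients with three visits each. The design matrix has 30 patient columns, 2 visit columns (3 and 6 months) and 1 treated column, 33 in all.

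- Single arm: the treated column equals the sum of the two visit columns. The rank is 32, the same as without the treated column.
- With a concurrent comparator group of 30 (60 patient + 2 visit + 1 treated = 63 columns), the rank is 63, so treatment can be estimated apart from visit.

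In the planned design the treatment coefficient is therefore the visit effect. Adding covariates changes what the visit effect is conditional on, but does not split it into drug and time. A linear time term would make the treatment term estimable only by assuming that background drift is linear, which three visits without a comparator cannot test.

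The regression covers capillaroscopy and the 24h recording, which includes PWV and AIx. Prothrombotic markers, the fourth primary outcome, are not named in it.

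**2. How large could one source of bias be?**

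Assumed inputs (none is in the document): share of patients with new or changed BP treatment 10-30%; reduction in 24h systolic BP in those patients 5-10 mmHg; SD of within-patient change 10 mmHg. From Sample size: n = 30 to 50.

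- Shift in the mean = share × reduction: 0.10 × 5 = 0.5 mmHg; 0.20 × 7.5 = 1.5 mmHg (midpoints); 0.30 × 10 = 3.0 mmHg.
- 95% CI half-width = t(0.975, n−1) × SD / √n: 0.373 × 10 = 3.7 mmHg at n=30; 0.284 × 10 = 2.8 mmHg at n=50.

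| Shift | Share of half-width, n=30 | Share of half-width, n=50 |
|---|---|---|
| 0.5 mmHg | 0.5/3.73 = 13% | 0.5/2.84 = 18% |
| 1.5 mmHg | 1.5/3.73 = 40% | 1.5/2.84 = 53% |
| 3.0 mmHg | 3.0/3.73 = 80% | 3.0/2.84 = 106% |

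Only the extreme case at n=50 reaches the half-width.

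The same point can be put as a false-positive rate, using exact noncentral-t power for a paired test at two-sided 0.05 (sidedness assumed). With no drug effect, a background drift of 0.1, 0.2 or 0.3 SD of the change is declared significant with probability 8.3%, 18.5% or 35.5% at n=30, and 10.7%, 28.4% or 54.8% at n=50, against 5% with no drift. The 3.0 mmHg extreme is 3.0/10 = 0.3 SD. A true drug effect of the same size gives the same probabilities, so the test cannot tell the two apart.

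**The case against.** Much of the operative text is already descriptive. The study is labelled observational, the primary outcome is a difference from baseline, and the regression is phrased as an association. The sentence on beneficial or negative effects stands in a motivational section and is hedged. This has force: that sentence is not a decision rule. But the verb in the aim and the closing claim about mediation are not hedged in the same way, and nothing in the article limits the causal reading.

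A reader might infer that the plan makes no attempt at adjustment and credits every change to the drug. The document does not support that. Statistical methods plans adjustment, and current treatment, DAS28, ESR and CRP are collected at each visit. The covariate list may properly sit in a document not shown. What stands is narrower: no covariate list can separate drug from time here.

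A reader might also treat falling inflammation as a rival explanation on a par with co-medication. The section on JAK inhibition credits these drugs with suppressing RA inflammation, so it is partly a mediator of the total effect. It becomes a problem for claims of pleiotropic effects and of mechanism, which require it to be separated.

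Finally, no passage says that 24h recordings lead to treatment changes. Bias from BP treatment is plausible, not documented.

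**Conclusion.** The point holds as a mismatch between design and claim. The study can estimate change after starting a JAK inhibitor. It cannot show that the drug induced the change, nor what mediated it. This follows from the structure of the design and needs no numerical assumption.

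The size of the BP bias does rest on assumptions: a shift of 0.5-3.0 mmHg against half-widths of 3.7 and 2.8 mmHg. It would be wrong to infer that this bias generally matches the sampling uncertainty. At the midpoints it is about 40-53% of the half-width, and at n=30 even the extreme falls short. The study remains worthwhile as a descriptive cohort. The stated conclusions should change.

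**What to change.** 1. **Wording.** In Aim of the study and both parts of Anticipated benefits, refer to change after starting a JAK inhibitor. State that causation and mediation cannot be shown, and allow an inconclusive result judged from the 95% CI.
2. **Regression.** In Statistical methods, define the term as the visit effect in a repeated-measures model and extend it to the prothrombotic markers. Report it with and without the co-medication recorded at each visit. Show adjustment for DAS28/CRP separately, labelled as possibly removing part of the drug effect because inflammation is a mediator.
3. **Sensitivity analysis for BP.** Add back a range of assumed effects (for example 5-15 mmHg, which spans and exceeds the 5-10 mmHg used above) to values recorded after a new or intensified antihypertensive. Do not set those values to missing, since that would selectively drop patients whose BP was high or rising. The article says current treatment is recorded but does not mention dose; identifying intensification needs dose, so confirm that it is captured.

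Steps 2 and 3 reduce bias from measured co-medication; only step 1 deals with time. The cost is a weaker claim and a little more analysis, largely on data already planned.
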